### Sample size estimation

This will be a two-arm cluster randomized controlled trial using villages as units of randomization. The minimum sample size for the baseline cross-sectional survey is estimated according to the methods proposed in the WHO STEPwise approach to chronic disease risk factors surveillance (STEPS) [34]. The sample size is calculated for 95% confidence intervals (CI) (z = 1.96) on the basis of a 5% margin of error and an estimated prior population prevalence of hypertension of 25.9% from the nation-wide representative STEPS survey in Tanzania [35], a design effect of 1 and an anticipated attrition rate of 20%. Participants will be adults aged 25–64 years and categorized into four age groups for each sex, resulting in eight strata. The resulting sample size is 2950. Participants with elevated blood pressure during the baseline survey will be eligible and invited to participate in the intervention study.

The sample size for the intervention study is calculated to provide an 80% power to detect a ≥ 6.5 mmHg difference in mean SBP between the intervention and control villages at an alpha level of 5%, assuming an attrition rate of 20%, an inter-cluster correlation of 0.03, and a standard deviation (SD) of SBP of 15 mmHg. The resulting sample size is 258 participants per arm of six villages. Thus, the total sample size for intervention study will be 516 participants from 12 villages.

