### Data analysis

#### Quantitative data

The statistical analyses will be conducted using IBM SPSS statistics version 20, following the Consolidated Standards for Reporting Trials (CONSORT) guidelines for cluster randomized trials [44]. In the initial analysis, baseline characteristics of participants in the intervention study will be compared between intervention and control arms to ensures an approximate balance in the distribution of both measured and unmeasured confounders. Primary analyses will follow the intention-to-treat principle at 12 months, where all participants will be analyzed in their assigned intervention arm regardless of whether they actually received the intervention or not. Participants who refuse/withdraw their consent to continue with study will be excluded from the final analyses.

The primary outcome for the study is continuous mean SBP measured at baseline and at the end of participant follow-up. Change in mean SBP between baseline and end of intervention will be analyzed using individual-level data to assess the effectiveness of CHWs’ interventions for the reduction of blood pressure in the intervention arm compared to control arm. Between-group and within-group differences in mean SBP will be calculated and compared using difference-in-differences (DID) methods [45]. This approach will compare changes in mean SBP between baseline and 12 months for intervention and control villages.

Thus, IMPACT = [Y_i (*t* = 12)_ – Y_i (*t* = 0)_] - [Y_c (t = 12)_ – Y_c (t = 0)_].

Where Y_i(t = 12)_ is mean SBP in the intervention villages at the end-line survey (12 months), Y_i(t = 0)_ is mean SBP in the intervention villages at baseline survey, Y_c(t = 12)_ is mean SBP in the control villages at the end-line survey (12 months); and Y_c(t = 0)_ is mean SBP in the control villages at the baseline survey.

Multi-level analysis with mixed-effects models will be used to account for inter-observer and intra-observer variations in the groups at different times (at baseline and at end-line assessments). The intervention effect size will be reported as mean differences with 95% CIs.

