Similar methods of DID will be used for the analysis of secondary outcomes including changes in mean DBP, changes in the proportion of other CVD risk factors, and changes in 10-year risk for CVD event. The 10-year risk for CVD event will be estimated using the Globorisk office charts [46] specific for Tanzania. The Globorisk office chart is a simple instrument which requires age, SBP, self-reported smoking status, and gender to predict one’s 10-year risk for CVD event. For participants in the intervention, changes in 10-year risk will be assessed by comparing the risk at baseline and end-line assessment.

Missing data and loss to follow-up are major issues of concern as they may compromise inferences of any trial. Efforts will be made during trial implementation to ensure complete follow-up and minimize missing data and loss to follow-up. During analysis, we will assess the magnitude and compare the baseline characteristics of participants lost to follow-up and those with end-line assessment data to see if there is any specific pattern of missing and loss to follow-up. Since there is no single universal method for handling missing data in trials [47], it is difficult to decide a priori the best way to handle missing data for this study. The decision to exclude missing data from final analysis or use multiple imputation analysis will be made after examining the magnitude and pattern of missing data. For all analyses, a two-sided *p* value of ≤ 0.05 will considered statistically significant.

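### The mixed model is assigned to observer variation; neither village nor village-by-time is named as a level, so the primary difference-in-differences is not tied to the variation that cluster randomisation creates

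*Protocol article*

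**What the plan says.** The Quantitative data section describes the primary analysis in three steps. First, "Change in mean SBP between baseline and end of intervention will be analyzed using individual-level data". Second, the effect is a difference-in-differences: the 12-month change in mean SBP in intervention villages minus that in control villages. Third, "Multi-level analysis with mixed-effects models will be used to account for inter-observer and intra-observer variations in the groups at different times", the times being the baseline and end-line assessments. Secondary outcomes are to be handled by similar difference-in-differences methods.

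Three other places bear on this:

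- Sample size estimation uses "an inter-cluster correlation of 0.03", with six villages and 258 participants per arm.
- Randomization and blinding calls the village the unit of randomisation. It then forms two groups of three villages in each district and assigns one group to each arm, so four bundles are assigned.
- The limitations paragraph of the Discussion mentions multilevel analysis with random effects, as a means of reducing the consequences of imbalance between intervention and control villages.

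The Quantitative data section also commits to the CONSORT guidance for cluster randomised trials.

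**The concern.** A cluster trial needs a multilevel model because people in the same village resemble each other and were allocated together. That is the reason the sample size carries an ICC. The analysis section gives the model a different task, variation between and within observers, which is a measurement matter. An observer effect cannot stand in for a village effect. The Blood pressure section averages three readings into one value for analysis, so the repeats that could show within-observer variation are gone. Baseline is measured by research assistants and end-line by an independent team, so observer may be largely tied to time point.

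The Discussion's use of random effects does not repair this. Random effects describe correlation and do not remove imbalance in age, sex or risk-factor pattern between arms.

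Naming a village random intercept alone would not be enough either. A stable village effect cancels from a change. What remains is the extent to which villages drift differently over 12 months, and that needs a village-by-time term. If it is left out, such drift can be read as an intervention effect on the primary outcome.

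**Working it through.** **Inputs from the protocol.** Sample size estimation gives "an 80% power to detect a ≥ 6.5 mmHg difference in mean SBP between the intervention and control villages", alpha 5%, "a standard deviation (SD) of SBP of 15 mmHg", ICC 0.03, attrition 20%, and 258 participants in six villages per arm. Quantitative data gives "a two-sided *p* value of ≤ 0.05 will considered statistically significant". Per village this is 258/6 = 43 enrolled and 43 × 0.8 = 34.4 analysed.

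**Inputs assumed.** Individual correlation over 12 months π = 0.5 to 0.6. Village autocorrelation ρ from 0.5 to 1.0. The documents give neither.

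**Step 1: reproduce 258.** For village size m with six villages per arm and t on 10 df, 6m = F[1 + (m − 1) × 0.03], where F = 2[15(2.228 + 0.879)/6.5]² = 102.8. Hence m = 0.97F/(6 − 0.03F) = 34.2. Dividing by 0.8 gives 42.8, rounded up to 43, and 6 × 43 = 258. Without clustering, 2[15(1.960 + 0.842)/6.5]² rounds up to 84, and 84/0.8 = 105. The article does not print its formula, but 258 follows exactly when clustering and cluster-based degrees of freedom are used.

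**Step 2: simple end-line contrast with clustering ignored.** Design effect = 1 + (34.4 − 1) × 0.03 = 2.00. The naive SE is 15√(2/206.4) = 1.48 mmHg and the correct SE is 1.48 × √2.00 = 2.09 mmHg. Type I error = 2[1 − Φ(1.96/√2.00)] = 16.6%. With all 43 enrolled the design effect is 2.26 and the error 19.2%, but that ignores the planned attrition.

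**Step 3: the planned difference-in-differences.** Between-village variance is 0.03 × 225 = 6.75 and within-village variance 0.97 × 225 = 218.25. For the change from baseline:

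- village part A = 2 × 6.75 × (1 − ρ)
- individual part B = 2 × 218.25 × (1 − π)
- true variance of a village mean change = A + B/34.4
- variance assumed when village is omitted but pairing is kept = (A + B)/34.4
- variance assumed with a village intercept but no village-by-time term = B/34.4
- type I error = 2[1 − Φ(1.96/√R)], with R = true/assumed

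Example, ρ = 0.5 and π = 0.5: A = 6.75, B = 218.25, B/34.4 = 6.34. With village omitted, R = 13.09/6.54 = 2.00 and the error is 16.6%. With intercept only, R = 13.09/6.34 = 2.06 and the error is 17.2%.

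| ρ | Village omitted (π = 0.5; 0.6) | Village intercept only (π = 0.5; 0.6) |
|---|---|---|
| 1.0 | 5.0%; 5.0% | 5.0%; 5.0% |
| 0.9 | 7.4%; 8.0% | 7.5%; 8.2% |
| 0.8 | 9.9%; 11.1% | 10.1%; 11.3% |
| 0.5 | 16.6%; 19.1% | 17.2%; 19.9% |

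**Step 4: pairing ignored as well.** The assumed SE is then √(4 × 225/206.4) = 2.09 mmHg. The true SE at ρ = 0.5 is 2.09 (π = 0.5) or 1.99 (π = 0.6), and type I error is about 5% or 4%. At ρ = 0.8 it is 1% to 2%. That analysis is not anti-conservative, only inefficient.

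**The case against.** A reader might infer that the trial's standard errors will ignore the cluster randomisation. The documents do not support that as fact. They commit to a multilevel mixed model and to the cluster extension of CONSORT, and the sample size reproduces only when clustering is used. A village random effect may well be intended and may be written in a full protocol or analysis plan that is not shown. Random-effect structure and degrees of freedom are often left to such a document, so their absence from an article is not itself a fault. This part of the objection stands.

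A reader might also take 17% to 19% as the type I error of the primary analysis. Those figures belong to a single end-line contrast, the upper one before attrition. In a difference-in-differences, stable village effects cancel, and the inflation can be nil. This also stands.

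What does not fall is the stated purpose. The article gives the model a task, and it is the wrong one for this design. The cluster CONSORT reference fixes no model term, and the Discussion's remark gives a second purpose that is also not within-village correlation.

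**Conclusion.** The sentence on the mixed model should be corrected. It names the wrong source of variation and leaves village and village-by-time unnamed, although the sample size depends on village clustering (258 per arm with it, 105 without).

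The consequence is conditional. If village-by-time variation is left out while participant pairing is modelled, type I error runs from 5% to about 20% over village autocorrelations from 1.0 to 0.5. This rests on the protocol's ICC and SD, 34.4 analysed per village, a normal reference distribution and the assumed individual correlation of 0.5 to 0.6. The calculation treats the 12 villages as independent clusters and so does not cover any correlation within bundles. Should-fix, moderate confidence.

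**What to change.** Replace the sentence on the mixed model with wording such as: *SBP at baseline and 12 months will be analysed in a mixed model with fixed effects for arm, time and their interaction, and random effects for village, village-by-time and participant. Inference on the interaction will use small-sample degrees of freedom based on the number of clusters.* A change-score model with a village random effect targets the same contrast more simply. A model for end-line SBP with a village random effect would also serve, but it departs from the printed IMPACT formula, so the text should then say so.

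Drop observer variation as the stated purpose of the model. Apply the same structure to DBP, and its counterpart for binary outcomes to the proportions.

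State whether the cluster is the village or the bundle of three. Degrees of freedom are 12 − 2 = 10 for villages but 4 − 2 = 2 for bundles, where the two-sided 5% critical value is 4.30.

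The cost is a few lines of text and wider intervals. With villages as clusters the sample size is unchanged: power is 80.0% at 34.4 per village, SE 2.09 mmHg and 10 df. With bundles, stated power falls sharply. Keeping the same SE (noncentrality 6.5/2.09 = 3.11) and using a noncentral t on 2 df, it is about 41%, before any added variance between bundles.

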##### Blood pressure

Blood pressure will be measured using a standardized digital blood pressure machine (OMRON HEM-712C). Blood pressure will be measured on the left arm with the participant in a seated position. The first reading will be taken after resting for at least 5 min. The second and third readings will be taken halfway and at the end of interview, respectively. An average of three readings will be used in the analysis. Participants with elevated blood pressure will have measurements repeated on the following days to confirm their elevated blood pressure. Hypertension will be defined as average SBP ≥ 140 mmHg and/or DBP ≥ 90 mmHg and/or current treatment with antihypertensive medications in accordance with the Seventh Report of the Joint National Committee on Prevention, Detection, Evaluation and Treatment of High Blood Pressure [38].

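### Ten-year CVD risk is given two analyses, one between arms and one before-after without a control; the second would include regression to the mean and the referral effect and cannot be read as an intervention effect

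*Protocol article*

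**What the plan says.** All references are to the protocol article.

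- **Analysis, first statement** (Quantitative data): "Similar methods of DID will be used for the analysis of secondary outcomes", and the list that follows includes "changes in 10-year risk for CVD event". The same section defines DID as the change in intervention villages minus the change in control villages.
- **Analysis, second statement** (same paragraph, after the description of the risk chart): "For participants in the intervention, changes in 10-year risk will be assessed by comparing the risk at baseline and end-line assessment". No control group appears, and neither statement is marked as the main or as a descriptive analysis.
- **The chart** (Quantitative data): a simple instrument "which requires age, SBP, self-reported smoking status, and gender".
- **Entry** (Sample size estimation): "Participants with elevated blood pressure during the baseline survey will be eligible and invited to participate in the intervention study". The Blood pressure section defines hypertension by SBP of at least 140 mmHg, diastolic pressure of at least 90 mmHg, "and/or current treatment with antihypertensive medications".
- **Readings** (Blood pressure): "An average of three readings will be used in the analysis". Elevated readings are repeated on later days for confirmation. Which occasion supplies the baseline value is not stated.
- **Referral** (The intervention, third component): referral notes go to people with elevated pressure in intervention and control villages alike.
- **Outcome definition** (Secondary outcomes, item 3): change from baseline in the proportion with 10-year risk above 30%. No comparator is named there, whereas the primary outcome names the control villages.

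**The concern.** The two statements are different estimates of the same secondary outcome. One subtracts the control arm's change and the other does not.

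The uncontrolled version is weak here for a specific reason. People are enrolled because a baseline reading was high, and SBP goes straight into the risk score. Part of each high reading is short-term variation that will not recur at 12 months, so average SBP, and the score with it, is expected to fall in an enrolled group left alone. Referral to a health facility, which both arms receive, may lower it further. A within-arm change mixes these with any effect of the community health workers and cannot separate them.

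The section also sets a two-sided 0.05 threshold for all analyses and does not exempt this comparison. If the single-arm sentence stands as written, a fall in the intervention arm could be tested and reported as a result for item 3 without reference to the control arm.

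**Working it through.** **What can be reproduced.** The plan gives no figure for the 10-year-risk analysis. Its only relevant input is the SD of SBP, 15 mmHg (Sample size estimation). That SD is consistent with the stated 258 per arm:

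- 258/6 = 43 per village, and 43 × 0.8 = 34.4 after attrition.
- Design effect 1 + 33.4 × 0.03 = 2.002.
- SE = √(2 × 15² × 2.002 / 206.4) = 2.09.
- With the planned difference of 6.5 and a t test on 10 df, power is 80.03%.

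So 15 is the SD the plan actually works with.

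**Regression to the mean in one arm.** Inputs:

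- SD 15 (protocol).
- Entry threshold of 140 for SBP (Blood pressure section), applied here as if it were the only route of entry.
- Population mean μ = 125 to 130 and test-retest correlation ρ = 0.6 to 0.9. Both are assumptions, because the protocol gives neither.

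For a normal distribution truncated below at 140, with a = (140 − μ)/SD, the expected fall with no intervention is

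fall = SD × (1 − ρ) × φ(a) / [1 − Φ(a)].

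- μ = 125: a = 1.00, ratio 1.525, SD × ratio = 22.9.
- μ = 130: a = 0.667, ratio 1.265, SD × ratio = 19.0.

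| ρ | Fall, μ = 125 (mmHg) | Fall, μ = 130 (mmHg) |
|---|---|---|
| 0.6 | 9.15 | 7.59 |
| 0.7 | 6.86 | 5.69 |
| 0.8 | 4.58 | 3.80 |
| 0.9 | 2.29 | 1.90 |

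The range is 1.9 to 9.2 mmHg. With an assumed SD of 20 it would be 2.3 to 10.6 mmHg.

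**The same mechanism under DID.** Two arms of six villages were simulated 4,000 times with no intervention effect: μ = 127, SD 15, ρ = 0.7, ICC 0.03, and entry at SBP of at least 140 in both arms.

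- Mean before-after change in the intervention arm: −6.4 mmHg.
- Mean DID: −0.01 mmHg. Its SD across runs was 0.96, so the simulation error of that mean is 0.96/√4000 = 0.015. The result cannot be told from zero.

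The two statements in the plan therefore have different expectations when nothing works: zero for one, a fall for the other.

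**What cannot be computed.** The risk chart is not in the document, so these SBP figures cannot be turned into a change in the proportion above 30%. The direction follows from SBP being an input. One year of ageing, also an input, works slightly the other way.

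**The case against.** The strongest defence is that the plan already contains the right analysis. Change in 10-year risk is named as a DID outcome. Both arms are enrolled by the same blood-pressure rule, villages are assigned after the baseline survey, and both arms have an end-line survey. Regression to the mean and the referral effect are then common to both arms and cancel in expectation. This stands. A reader might infer that the trial's result for this outcome will show a false benefit; the document does not support that, because it does not make the before-after comparison the only or the main analysis.

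It can also be said that the disputed sentence merely explains how each person's change is formed before DID is applied, and that it announces no test. Elsewhere the article speaks of participants in the intervention study and means both arms (Participants and eligibility criteria, End-line survey). But this sentence lacks the word study, and the Follow-up section uses the fuller phrase for people visited by community health workers, who are in the intervention arm only. The wording does not settle the matter, which is itself a reason to fix it.

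Two further inferences fail:

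- **That SBP is also to be judged before-after**, because the section says "Between-group and within-group differences in mean SBP will be calculated". The sentence goes on to say that these differences are compared by DID, and the formula that follows subtracts one arm's change from the other's. The primary analysis is not touched.
- **That the average which qualifies a person is also the analysis baseline.** The article does not say which occasion is used. If the confirmatory readings serve as baseline, the expected fall is smaller.

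**Conclusion.** The point holds as a conflict of wording with a real consequence for one of the two analyses. The single-arm comparison of 10-year risk cannot be read as an intervention effect; the DID of the same outcome can, as far as regression to the mean and the common referral are concerned.

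The size, an SBP fall of about 1.9 to 9.2 mmHg with no intervention, is an illustration. It rests on the protocol's SD of 15, on an assumed population mean and test-retest correlation, and on entry through SBP alone. People who qualify by diastolic pressure or by treatment would show a smaller fall, so the figure for the mixed group is lower. A reader may be tempted to set this range against the SBP difference the trial is powered for. That comparison is not valid, because the primary outcome is analysed between arms.

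The matter concerns one secondary outcome, and it is worth correcting because the correction is so small.

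**What to change.** 1. Delete the single-arm sentence, or reword it to say that within-arm change in 10-year risk is shown descriptively for each arm, with no p-value and no claim of effect.
2. State that the effect on 10-year risk, and on the proportion above 30%, is estimated only as a between-arm contrast that accounts for village clustering. The DID already stated is acceptable. The 12-month value adjusted for baseline is preferable, because it also handles chance differences in baseline risk between a small number of villages; this is a preference and not the correction of an error.

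The cost is one or two sentences. No new data, visits or sample size are needed, since both arms already have baseline and end-line surveys.

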#### Qualitative data

Analysis of qualitative data from the FGDs will be done using Nvivo 9® software and manual coding. The audio recordings from FGDs will be transcribed verbatim and translated into English. Caution will be taken to ensure that no data will be lost during translation. The text data will be entered into Nvivo 9® software and analyzed for themes on perceptions about quality and acceptability of the CHWs intervention in the community.

### Handling and storage of data

Participants will be assigned unique study identification numbers for data collection. Except for consent forms, which will bear the name and signature of the participant; all other information will be collected using unique study participants’ identification numbers. All paper forms will be double-entered into a password-protected computer by trained data entry clerks. The data will be transferred daily to a secure server where the data manager will review the entered data for quality assurance and quality control. Entered paper forms will then be stored and locked at a central office, with access to the files granted only to the study’s principal investigator and key personnel. Any reports or publications or scientific presentations will not contain any participants’ identifying information.

